## 2.4 Outcome Measures

Assessments will be conducted by professional rehabilitation therapists blinded to group allocation at baseline (pre-intervention) and immediately after the 6-week intervention period.

### 2.4.1 Primary Outcome Measure:

1. Lower Limb Motor Function: Assessed using the Fugl-Meyer Assessment for Lower Extremities.

### 2.4.2 Secondary Outcome Measures:

1. Walking Function: Assessed using the Functional Ambulation Classification.
2. Gait Analysis: Using a three-dimensional motion capture and force plate system to quantitatively analyze spatiotemporal parameters (e.g., gait speed, stride length, cadence) and kinematic parameters (e.g., angular changes of hip, knee, and ankle joints during the gait cycle) of the affected side.

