Stimulation, which focuses on "central modulation" and "neuroplasticity regulation," may produce synergistic effects. This combined intervention strategy is expected to simultaneously address both peripheral sensory input and central neuromodulation, promoting a more comprehensive recovery of lower limb motor function after ICH. However, there is a lack of high-quality clinical evidence regarding the combined application model and definitive efficacy of these two innovative techniques.

Therefore, this study aims to systematically evaluate the effects of Transcutaneous Auricular Vagus Nerve Stimulation combined with Repetitive Facilitative Exercise on lower limb motor function, walking ability, and gait parameters in patients during the recovery phase of ICH through a randomized controlled trial. The goal is to provide a new, evidence-based multimodal combined intervention strategy for ICH rehabilitation.

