## 2.6 Statistical Analysis Methods

Data analysis will be performed using SPSS software. Continuous data conforming to a normal distribution will be presented as mean  $\pm$  standard deviation and compared between groups using independent samples t-tests; within-group comparisons (pre- vs post-intervention) will use paired samples t-tests. Continuous data not conforming to a normal distribution will be presented as median (interquartile range) and analyzed using non-parametric tests. Categorical data will be analyzed using chi-square tests. All statistical tests will be two-sided, with a P-value  $< 0.05$  considered statistically significant.

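### The gait outcome is an open list of examples and every test is called significant at P<0.05, so the false positive risk for gait is well above 5% and cannot be bounded

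*Protocol*

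**What the plan says.** The protocol has one primary outcome, lower-limb motor function (section 2.4.1: "Assessed using the Fugl-Meyer Assessment for Lower Extremities"). Section 2.4.2 lists two secondary outcomes. The first is a single scale ("Walking Function: Assessed using the Functional Ambulation Classification"). The second is a three-dimensional gait analysis, defined as "spatiotemporal parameters (e.g., gait speed, stride length, cadence) and kinematic parameters (e.g., angular changes of hip, knee, and ankle joints" over the gait cycle. Both parts of the gait definition are lists of examples. Three spatiotemporal parameters and three joints are named, none is marked as the key one, and the text does not say which feature of a joint-angle curve is to be compared.

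Section 2.6 sets one rule for everything: "All statistical tests will be two-sided, with a P-value" below 0.05 counting as significant. Normally distributed continuous outcomes are "compared between groups using independent samples t-tests". Section 2.6 draws no line between primary, secondary and exploratory tests. Section 1 states the aim as the effect on "lower limb motor function, walking ability, and gait parameters in patients during the recovery phase of ICH", so gait stands beside motor function in what the trial sets out to show.

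**The concern.** A 5% threshold gives a 5% error rate for one test. Applied to each of several gait parameters, it gives a higher chance that at least one crosses the line when the stimulation does nothing for gait. Because the parameters are given as examples, the text also leaves room to decide which ones to analyse or report after the motion-capture data have been seen. Assessor blinding (section 2.4) protects the measurements but not that later choice.

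At stake is the gait part of the aim. A report could truthfully say that a gait parameter improved significantly under the protocol's own rule, and a reader could not tell how many parameters that one was drawn from.

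**Working it through.** **The plan's own figure.** Section 2.2.1 assumes d = 0.8, two-sided alpha 0.05 and power 0.80 for FMA-LE. The exact two-sample t calculation gives 25.52, hence 26 per group. Allowing for 10% dropout, 26 / 0.9 = 28.9, hence 29 per group and 58 in total. The stated figures reproduce and are not affected by this point. The primary outcome is one between-group test at 0.05.

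**Counting the secondary comparisons.** There is one post-treatment assessment (section 2.4), so one between-group comparison per parameter is assumed.
- Spatiotemporal items named: 3.
- Joints named: 3, taking one angle measure per joint, which is the smallest reading.
- Named gait items: 3 + 3 = 6. With FAC: 7.

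**Independent tests.** If all null hypotheses are true, the chance of at least one P<0.05 among k tests is 1 − 0.95^k.
- k = 6: 1 − 0.95^6 = 0.265
- k = 7: 1 − 0.95^7 = 0.302

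**Correlated tests.** Gait measures from the same patient are correlated, and the protocol gives no correlations, so a range is assumed. The table comes from simulated two-sample t-tests with 26 per group, a common correlation between outcomes and no true effect on any of them (20,000 to 40,000 runs per cell).

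| Common correlation | 6 gait items | 7 items (with FAC) |
|---|---|---|
| 0 (formula) | 26% | 30% |
| 0.3 | 24% | 27% |
| 0.5 | 21% | 23% |
| 0.7 | 17% | 18% |
| 0.9 | 11% | 11–12% |

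FAC is a classification and was treated as a continuous outcome here, so the seven-item column is approximate.

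**What the open list adds.** The number of parameters beyond those named is unknown. By the same formula, 13 independent tests give 1 − 0.95^13 = 0.487 and 14 give 1 − 0.95^14 = 0.512. The risk passes one half only at 14 independent parameters, and later if they are correlated. The protocol neither states nor excludes such a number.

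**The case against.** **This is SAP material.** A detailed list of motion-capture parameters and the handling of multiplicity are often left to the SAP, and one may exist. A mere absence of either would not be a fault in the protocol. What stands is narrower. Section 2.6 states that every test below 0.05 is significant, and section 2.4.2 states an outcome by example. An SAP that adjusted the gait tests or called them exploratory would have to depart from section 2.6 as written.

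**A 0.05 level for secondary outcomes is conventional.** True, and the trial is sized on a single primary outcome whose error rate is intact. This limits the point to secondary claims. It does not remove it, because gait is named in the aim and nothing marks these results as exploratory.

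**Stronger readings that the protocol does not support.**
- A reader might infer that a false positive gait result is likely. For the named items the chance is 11% to 26%. Even odds need at least 14 independent parameters, a count that appears nowhere in the protocol.
- A reader might infer that the parameters will be picked after the data are seen. The open list permits this, but the protocol does not say so.
- A reader might add the pre-post tests ("within-group comparisons (pre- vs post-intervention) will use paired samples t-tests") and count three tests for each of eight outcomes, 24 in all. That count includes the primary outcome and assumes paired tests for FAC, which section 2.6 does not clearly assign. More importantly, within-arm tests do not test the stimulation. Both arms receive the exercise programme (section 2.3), so a pre-post change can be real when the stimulation has no effect. These tests do not belong in this error rate.

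**Conclusion.** The point holds for the secondary gait outcomes only, as a cheap improvement. On the items the protocol names, the chance of at least one false positive gait result is about two to five times the nominal 5%. This rests on one measure per named item, one between-group comparison each, no true effect on any gait parameter, and an assumed common correlation between 0 and 0.9. Because the list is open, the protocol sets no ceiling on this risk.

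**What to change.** Before any unblinded data are examined:
1. Replace the examples in section 2.4.2 with a closed list of gait parameters, stating for each joint which angle measure is meant.
2. Name one key gait outcome. Gait speed, already listed, is a natural candidate.
3. Amend the significance sentence in section 2.6 so that two-sided 0.05 applies to the primary outcome. If formal secondary claims are wanted, add that FAC and the key gait outcome are tested only after a significant primary result, using Holm at an overall 0.05: the smaller P-value against 0.025 and, if that is met, the larger against 0.05.
4. Report all other gait parameters as exploratory, with between-group estimates and 95% confidence intervals and no claim of significance.

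A simpler acceptable alternative is to label all secondary outcomes exploratory and leave out the Holm step.

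**Cost.** A few sentences, with no change to the sample size or the measurements. There will be fewer nominally significant secondary results. If the ordered testing is used, no formal gait claim is possible when the primary is not significant. At the stated 80% power that happens about 1 − 0.80 = 20% of the time even if the assumed effect on FMA-LE is real.

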## 2.5 Safety Monitoring

Any adverse events occurring during the study period, such as skin irritation, dizziness, discomfort, or falls, will be recorded and analyzed for their relationship to the interventions.

## 2.6 Statistical Analysis Methods

Data analysis will be performed using SPSS software. Continuous data conforming to a normal distribution will be presented as mean  $\pm$  standard deviation and compared between groups using independent samples t-tests; within-group comparisons (pre- vs post-intervention) will use paired samples t-tests. Continuous data not conforming to a normal distribution will be presented as median (interquartile range) and analyzed using non-parametric tests. Categorical data will be analyzed using chi-square tests. All statistical tests will be two-sided, with a P-value  $< 0.05$  considered statistically significant.

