### **2.2 Study Participants**

**2.2.1 Sample Size Estimation:** Based on preliminary trial results, using the sample size calculation formula for comparing means between two independent samples, with the primary outcome measure (FMA-LE score) expected effect size  $d=0.8$ ,  $\alpha=0.05$

(two-tailed), and power  $1-\beta=0.8$ , an estimated 26 participants per group is required. Considering an approximate 10% dropout rate, 29 participants per group are planned, totaling 58 participants.

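### The primary FMA-LE comparison does not adjust for baseline FMA-LE; the stated test is valid, but ANCOVA would give more precision at almost no cost

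*Protocol*

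**What the plan says.** The primary outcome is lower limb motor function, "Assessed using the Fugl-Meyer Assessment for Lower Extremities" (Protocol 2.4.1). Assessments take place "at baseline (pre-intervention) and immediately after the 6-week intervention period" (2.4), so the plan provides for a baseline value of the primary outcome in each patient.

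Section 2.6 gives one rule for all continuous data. If normal, they are "compared between groups using independent samples t-tests". If not, the rule is: "Continuous data not conforming to a normal distribution will be presented as median (interquartile range) and analyzed using non-parametric tests". Baseline is expressly used only in the comparisons inside each arm: "within-group comparisons (pre- vs post-intervention) will use paired samples t-tests". Those do not compare the arms. No covariate or adjusted model is named, and the text does not say whether the between-group test is applied to the week-6 score or to the change from baseline. Section 3.3 adds only that efficacy is judged from data gathered before and after treatment.

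Section 2.2.1 sizes the trial "using the sample size calculation formula for comparing means between two independent samples", with d = 0.8, two-sided alpha 0.05 and power 0.8, and concludes that "an estimated 26 participants per group is required". That becomes 29 per group, 58 in all, after about 10% dropout. It does not say whether d is in units of the week-6 SD or the SD of change.

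**The concern.** The baseline value of a functional score usually predicts the later value of the same score. A between-group test that leaves it out treats the predictable part of the variation between patients as noise. In a trial of this size that can cost precision in two ways: a wider confidence interval than necessary, and an observed difference that carries along part of any chance difference between the arms at baseline. Section 2.1 describes no stratification by baseline function that would limit such differences.

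A change-score test recovers part of this but fixes the weight on baseline at one. ANCOVA estimates the weight from the data. At stake is the precision of the primary estimate, not its validity.

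**Working it through.** **Inputs.** From Protocol 2.2.1: d = 0.8, two-sided alpha 0.05, power 0.80, n = 26 per arm, 10% dropout. Not in the document and therefore assumed: the baseline-to-week-6 correlation, r = 0.3, 0.5, 0.7 or 0.8, and equal SDs at both times and in both arms.

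**1. Reproduce the plan's figure.** The normal approximation gives 2 × (1.960 + 0.842)² / 0.8² = 24.5, so 25 per arm. The noncentral-t calculation gives 25.52, so 26. Dropout: 26 / 0.9 = 28.9, so 29 per arm and 58 in total. The stated size reproduces.

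**2. Power with 26 per arm, d = 0.8 on the week-6 SD.** Power comes from a noncentral t distribution with noncentrality (standardised effect) × √(26/2), where √13 = 3.606.

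- Week-6 t-test: effect 0.8, noncentrality 2.884, 50 df.
- Change-score t-test: the SD of change is SD × √(2(1 − r)), so the effect is 0.8 / √(2(1 − r)), 50 df.
- ANCOVA: the residual SD is SD × √(1 − r²), so the effect is 0.8 / √(1 − r²), 49 df.

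| r | Week-6 t-test | Change t-test: effect, power | ANCOVA: effect, power |
|---|---|---|---|
| 0.3 | 0.81 | 0.676, 0.67 | 0.839, 0.84 |
| 0.5 | 0.81 | 0.800, 0.81 | 0.924, 0.90 |
| 0.7 | 0.81 | 1.033, 0.95 | 1.120, 0.98 |
| 0.8 | 0.81 | 1.265, 0.99 | 1.333, 0.997 |

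Allowing for the small loss from estimating the baseline slope (noncentrality × √(48/49)) lowers the ANCOVA figures by less than one point. A simulation of 20,000 trials gave 0.898, 0.975 and 0.997 at r = 0.5, 0.7 and 0.8.

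The ANCOVA gain over a week-6 t-test is therefore about 3 points at r = 0.3, 10 at 0.5, 17 at 0.7 and 19 at 0.8. Over a change-score t-test it is large at low r (about 18 points at 0.3) but only about 2 points at r = 0.7 and less at 0.8.

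**3. If d = 0.8 is in change-score units and change is tested.** The t-test power is 0.807 for every r. The effect for ANCOVA is 0.8 × √(2(1 − r)) / √(1 − r²) = 0.8 × √(2 / (1 + r)). At r = 0.7 this is 0.868, power 0.866, a gain of about 6 points. At r = 0.8 it is 0.843, power 0.846, a gain of about 4 points.

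**4. Chance baseline imbalance.** The standard error of the baseline difference is √(2/26) = 0.28 SD. An imbalance of one standard error moves the unadjusted week-6 difference by r × 0.277 SD: 0.14 SD at r = 0.5, 0.19 at 0.7 and 0.22 at 0.8.

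**The case against.** The strongest reply is that nothing stated is wrong. The planned test matches the sample-size formula, the size reproduces, and under randomisation the unadjusted comparison is unbiased on average with valid type I error. The imbalance in step 4 is conditional on the sample drawn, and the t-test's standard error already allows for it. All of this stands, and it limits the point to precision.

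The gain also depends on what the document leaves open. If change is tested, baseline is already partly used, so it cannot be said flatly that the comparison ignores baseline. At r of 0.7 or more, ANCOVA then adds very little when d is on the week-6 SD. The eligibility floor in 2.2.2 (Brunnstrom stage III or above, Functional Ambulation Classification level 2 or above) narrows the range of baseline function and could lower r. At r = 0.3 the gain over a week-6 test is only about 3 points.

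A reader might infer two stronger charges. Neither is supported.

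- **Inflated type I error from a choice between week-6 and change scores.** That describes an analyst who runs both and keeps the better result. The protocol plans no such thing, and the analysis variable may be settled in a statistical analysis plan that is not shown.
- **A primary test picked after seeing the data.** Section 2.6 states its rule in advance: a t-test if normal, otherwise "analyzed using non-parametric tests". A simulation of one version of that rule (Shapiro-Wilk, then t-test or Mann-Whitney, 26 per arm, 10,000 runs) gave type I error of 4.8% to 5.2%. No harm to type I error is shown.

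The possible existence of a separate plan does not remove the point, because the protocol itself names an unadjusted method.

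**Conclusion.** The point holds as a recommendation on efficiency. The stated primary comparison is valid and correctly sized, but it adjusts for no covariate when the best candidate is already being collected. With 26 per arm, ANCOVA has higher power than either unadjusted test at every r examined. The gain runs from less than one point (against a change-score test at r = 0.8, with d on the week-6 SD) to about 19 points (against a week-6 test at the same r). In the change-unit reading it is about 4 to 6 points at r of 0.7 to 0.8.

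Confidence is high that ANCOVA is the better choice, and lower about the size of the gain. That size rests on the assumed r, equal SDs, and the unstated scale of d.

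**What to change.** In section 2.6, name the primary analysis as ANCOVA: week-6 FMA-LE regressed on randomised group with baseline FMA-LE as covariate. Report the adjusted mean difference with 95% CI and two-sided P. Keep a rank-based or bootstrap version as a sensitivity analysis. With baseline as covariate, modelling the week-6 score or the change gives the same group effect, so this also settles which of the two is tested. The same form can be used for the continuous gait parameters.

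The cost is one paragraph of text and one degree of freedom. It needs no extra patients, visits or data, SPSS (already named in 2.6) can run it, and the sample size can stay as it is. The change should be made before any outcome data are examined by group.

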#### 2.2.2 Inclusion Criteria:

1. Diagnosis of supratentorial ICH confirmed by CT or MRI, with stable vital signs and neurological function;
2. Disease duration of 1-6 months (recovery phase);
3. Age 18-75 years;
4. Presence of unilateral lower limb motor dysfunction (Brunnstrom stage of the affected lower limb  $\geq$  III);
5. Ability to walk short distances with minimal assistance or supervision (Functional Ambulation Classification  $\geq$  level 2);
6. Clear consciousness, able to understand and cooperate with assessments and treatments;
7. Signed informed consent from the patient or their legal guardian.

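### Section 2.6 has no rule for ordered outcomes, so on its plain text the Functional Ambulation Classification is compared by a chi-square test that ignores the order of its levels

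*Protocol*

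**What the plan says.** Protocol section 2.6 sorts data into three routes. Normally distributed continuous data get t-tests. Continuous data that are not normal are "analyzed using non-parametric tests", with no test named. For the rest, "Categorical data will be analyzed using chi-square tests". There is no separate route for ordered categories. It adds that "All statistical tests will be two-sided", at the 0.05 level.

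Section 2.4.2 lists as its first secondary outcome "Walking Function: Assessed using the Functional Ambulation Classification". It does not say whether FAC counts as continuous or categorical. Section 2.2.2 admits patients at FAC level 2 or higher, described as "Ability to walk short distances with minimal assistance or supervision". The top of the scale and the expected distribution over levels are not given.

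On numbers, section 2.2.1 says that "an estimated 26 participants per group is required" for the primary outcome, raised to 29 per group for about 10% dropout.

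On safety, section 2.5 says that events "such as skin irritation, dizziness, discomfort, or falls" "will be recorded and analyzed for their relationship to the interventions". No comparison of event counts between arms is stated.

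**The concern.** FAC is a classification in ordered levels. Because section 2.6 reserves its non-parametric route for continuous data, the natural reading of the text sends FAC to chi-square.

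Pearson's chi-square on a levels-by-arm table gives the same statistic whichever way the levels are permuted. It spreads its sensitivity over all patterns of difference (3 degrees of freedom with four levels), although the trial asks about one pattern, a shift towards better walking. A significant result would not by itself say which arm walked better. A real shift of moderate size would be missed more often than with a test that uses the order.

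At stake is a secondary conclusion on walking ability, one of the effects that section 1 sets out to evaluate.

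**Working it through.** **1. The plan's own sample size.** Inputs from section 2.2.1: d = 0.8, two-sided alpha 0.05, power 0.80. The normal approximation is n = 2(1.960 + 0.842)²/0.8² = 24.5, so 25 per group. The exact t-test needs 25.52, so 26 per group, with power 80.7%. For dropout, 26/0.90 = 28.9, so 29 per group. The stated figures are reproduced. The check below uses 26 evaluable per arm.

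**2. Assumptions that the protocol does not supply.** FAC at 6 weeks occupies three, four or five levels. The treatment effect is a common odds ratio (OR) of 2, 3 or 4. Both are assumptions, so ranges are shown.

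**3. One case by formula.** Take a control distribution of 10/30/40/20% and OR = 3.
- The control odds of being above each cut are 0.90/0.10 = 9, 0.60/0.40 = 1.5 and 0.20/0.80 = 0.25.
- Multiplied by 3 they are 27, 4.5 and 0.75, which are probabilities 0.964, 0.818 and 0.429.
- The treated distribution is therefore 3.6/14.6/39.0/42.9%.
- Chi-square: the non-centrality is 26 × Σ(p − q)²/(p + q) = 26 × (0.0305 + 0.0531 + 0.0001 + 0.0831) = 4.34. With 3 degrees of freedom and critical value 7.815, power is about 39%.
- Rank test: z = ln(3) × √[52 × (1 − Σp̄³)/12], where p̄ is the mean of the two arms' proportions. Σp̄³ = 0.104, so z = 1.099 × √(52 × 0.896/12) = 2.16. Power is Φ(2.16 − 1.96), about 58%.

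**4. Simulation.** 26 per arm, 3,000 trials per row, Pearson chi-square against Mann-Whitney with ties. The simulation standard error is about √(0.4 × 0.6/3000) = 0.9 points.

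| Control distribution (%) | OR 2: chi-square / rank | OR 3: chi-square / rank | OR 4: chi-square / rank |
|---|---|---|---|
| 15/35/35/15 | 17.5 / 26.4 | 38.0 / 55.5 | 57.9 / 76.0 |
| 10/30/40/20 | 16.1 / 26.4 | 35.7 / 55.4 | 56.8 / 75.2 |
| 25/25/25/25 | 16.5 / 26.4 | 40.0 / 56.8 | 60.2 / 75.2 |
| 5/45/45/5 | 13.7 / 24.4 | 32.7 / 49.3 | 50.9 / 70.2 |
| 5/20/35/25/15 | 14.4 / 27.7 | 34.7 / 59.0 | 53.9 / 77.5 |
| 30/45/25 | 18.9 / 25.4 | 43.8 / 54.4 | 63.3 / 73.6 |

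At OR 3 the loss runs from 54.4 − 43.8 = 10.6 points (three levels) to 59.0 − 34.7 = 24.3 points (five levels). A separate simulation on four-level distributions gave 37-42% against 55-58% at OR 3, and 55-60% against 73-78% at OR 4. The small differences from the table reflect simulation error and the distributions chosen.

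**5. Is chi-square invalid in these tables?** With equal arms, an expected count is below 5 when fewer than 10 patients in total sit in a level. With no true difference, that happens in 48% (even spread) to over 95% (peaked spreads) of four-level tables, and in 16% with three levels. Even so, the false-positive rate of chi-square is 0.034-0.052 across the six distributions.

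**6. Binary events.** Enumerating all 2×2 tables at a nominal 0.05 gives these true false-positive rates at 29 per arm:

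| Assumed event rate | Uncorrected chi-square | Fisher |
|---|---|---|
| 1% | 0.0003 | below 0.0001 |
| 5% | 0.027 | 0.001 |
| 10% | 0.054 | 0.009 |
| 20% | 0.048 | 0.021 |

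The largest value for uncorrected chi-square over the rates tried, at 26 or 29 per arm, is 0.056.

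**The case against.** The strongest reply is that the protocol never calls FAC categorical. The primary outcome, the lower-limb Fugl-Meyer score, is itself a score, and section 2.2.1 sizes it by a comparison of means. A team that treats FAC in the same way would find it non-normal and use a non-parametric test, with no loss. This stands as a limit on the size of the point, but it does not remove it. Section 2.6 confines that route to continuous data, and a classification in levels is categorical on its face. If both readings are open, the FAC test is not fixed in advance, and the same sentence cures that.

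A second reply is that an analysis plan not shown here may settle the test for a secondary outcome. It may. The point, however, concerns a rule that the protocol does state and that fits an ordered outcome badly.

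Third, the distributions and odds ratios are assumed, and with three occupied levels the loss is near the bottom of the range. Section 2.4.2 also lists gait speed, stride length and cadence, which are continuous and untouched. All of this stands.

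A reader might go further and infer that chi-square is invalid at these counts, or that it overstates adverse-event differences. Single tables tempt one to say so: for 4/29 against 0/29, uncorrected chi-square gives P = 0.038 and Fisher 0.112. The documents and the arithmetic do not support it. The true false-positive rate stays near or below 0.05, the gap largely reflects Fisher's conservatism, and section 2.5 states no between-arm test of adverse events.

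**Conclusion.** The point holds in limited form. Section 2.6 lacks a rule for ordered outcomes, and its plain text gives FAC a test that discards order and direction. At 26 evaluable per arm and an odds ratio of 3, this costs about 10 to 24 percentage points of power over three to five levels. It costs nothing if FAC is in practice handled as non-normal continuous data.

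The size rests on assumed FAC distributions and on a proportional-odds shift, since the protocol gives neither. The direction does not depend on one choice: a loss appeared in every scenario with a true effect. FAC is a secondary outcome, and the primary analysis and its sample size are unaffected. No finding is made on the safety analysis.

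**What to change.** Add one sentence to section 2.6: FAC at 6 weeks will be compared between arms with a proportional-odds model on arm and baseline FAC, or with a Mann-Whitney test (stratified by baseline FAC if feasible), and not with chi-square. One of the two should be chosen before any outcome data are seen.

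The cost is that sentence. FAC is already assessed at baseline and after the 6 weeks, so no new data, visits or patients are needed.

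Fisher's exact test for tables with small expected counts is optional. It removes the choice between versions of the test, but it is more conservative and would make a real imbalance in adverse events harder to detect.
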